#### WHO Quality of Life - BREF (WHOQOL-BREF; [28])

WHOQOL-BREF is one of the most widely used assessments of quality of life. In the current study, we will use the global item of the instrument (How would you rate your quality of life), answered on a 5-point Likert scale.

Post-intervention assessment will take place immediately after the intervention is completed and will include the same measures, as well as the Client Satisfaction Questionnaire-8 (CSQ-8; [21]). The assessments will be completed online, using the Qualtrics platform. We will also perform one follow-up assessment six months later, using the same measures and the Structured Clinical Interview for DSM-5 to compare the OCD diagnostic incidence.

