### Statistical analyses

#### Data analysis

Demographic and clinical data will be reported as means and SDs for continuous parametric data, medians, and ranges for non-parametric data, and frequencies and percentages for categorical data. Only two authors will have access to the final trial dataset. To illustrate participant flow, we will report results in a CONSORT diagram. Data analysis will be conducted using SPSS for Windows version 25. Given the anticipated dropout rate, mixed models will be employed as the most suitable statistical method. This approach is well-suited for analyzing repeated measures, accounting for the dependency between observations and handling missing data effectively. Mixed models will be adjusted for baseline values of the repeated measures. Descriptive statistics will be generated to summarize the means and proportions of baseline clinical and demographic variables across treatment conditions, allowing for the assessment of potential imbalances. Fixed effects in the model will include time, treatment, and their interaction. In cases of missing data, these variables will also be included as fixed effects. The significance of the time*treatment interaction p-values for various outcome measures will be assessed using the Benjamini–Hochberg procedure (two-sided p < 0.05). Time will be treated categorically, with the first post-baseline measurement serving as the reference category. To address the correlation among repeated measurements, a first-order autoregressive (AR (1)) structure will be imposed on the residuals. Furthermore, the interaction effect between time and group will be explored by analyzing estimated marginal means at different time points. We anticipate a significant interaction effect between time and group, signifying differential changes in scores over time between the two treatment conditions. Specifically, we expect a more pronounced decline in scores over time in the prevention group compared to the control group. To assess the statistical significance of improvements in the treatment conditions, a least significant difference test will be conducted with estimated marginal means to compare changes between groups. Linear mixed models are expected to reveal a statistically significant decline in the prevention condition from pretest to post-test, with no significant differences between post-test and follow-up measures. To facilitate comparisons with other studies, Cohen’s d statistic will be calculated to determine within-group effect sizes. In cases where the proportion of missing data exceeds 10%, maximum likelihood imputations will be performed based on demographics and pretreatment scores. Additionally, the proportions of dropouts and diagnostic incidence (from pre-test to follow-up) in the two treatment groups will be compared using the chi-square test.

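### Under the stated model, the only p-values placed under the Benjamini-Hochberg rule test whether the arm difference changes after the programme, not whether there is one

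*Protocol article*

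**What the plan says.** All of the following is in the Data analysis section of the protocol article unless another place is named.

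- Baseline handling: "Mixed models will be adjusted for baseline values of the repeated measures".
- Model terms: "Fixed effects in the model will include time, treatment, and their interaction".
- Time coding: "Time will be treated categorically, with the first post-baseline measurement serving as the reference category".
- Significance rule: "The significance of the time*treatment interaction p-values for various outcome measures will be assessed using the Benjamini–Hochberg procedure (two-sided p < 0.05").
- Visits after baseline: "Post-intervention assessment will take place immediately after the intervention is completed and will include the same measures" (end of the outcome measures section), followed by a single follow-up assessment.
- Expected results: a significant interaction, read as a steeper decline in the prevention group. For the prevention condition, the section also expects a decline from pretest to post-test, "with no significant differences between post-test and follow-up measures".
- Other comparisons: a least significant difference test on estimated marginal means, to compare change between the arms. The Abstract also names a MANOVA for group differences.
- Effect size: Cohen's d, of which the text says that the "statistic will be calculated to determine within-group effect sizes".

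**The concern.** The hypothesis in the aims section is superiority over the waitlist in symptom reduction. The matching quantity is a between-arm difference at a visit after the programme. When baseline is a covariate and time starts after it, that difference at post-test is carried by the treatment coefficient. The interaction carries only the later change in that difference.

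The significance rule names the interaction and not the treatment coefficient. The error-controlled test therefore does not address the hypothesis. The paragraph also pulls against itself: it expects a significant interaction and, in the prevention arm, no change after post-test. With a stable control arm, the second expectation makes the first false under the stated model.

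The only effect size named is within-group, so no planned effect size measures the contrast that randomisation makes interpretable.

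**Working it through.** **1. What the interaction is.** Let D1 be the baseline-adjusted arm difference at post-test and D2 the same at follow-up. With two time levels and post-test as reference:

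- treatment coefficient = D1
- time-by-treatment coefficient = D2 − D1, with 1 degree of freedom

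The choice of reference level alone does not alter the overall interaction test. What fixes its meaning is that baseline is a covariate and not a time level.

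**2. The plan's own pattern.** If the prevention arm does not change after post-test and the control arm is stable, D2 = D1. The interaction is then 0 for any size of D1.

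**3. Inputs.** From the Sample size section: d = 0.3 and 100 per arm. Alpha is two-sided 0.05, from the significance rule. Assumed, because the article gives none: outcome SD 1, correlation r between adjacent visits of 0.5 or 0.7, no dropout. The article states no power for the interaction, so there is no figure to reproduce for this test. The stated total of 175 is not used here. It does not follow from its stated inputs as a comparison of two means, which is a separate matter.

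**4. Formulas.**

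- SE of the baseline-adjusted difference at post-test = √(1 − r²) × √(2/100)
- SE of the interaction = √(2(1 − r)) × √(2/100)
- Power ≈ Φ(effect/SE − 1.96)

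**5. Arm difference at post-test, d = 0.3.**

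- r = 0.5: SE = 0.866 × 0.1414 = 0.122; z = 2.45; power 69%
- r = 0.7: SE = 0.714 × 0.1414 = 0.101; z = 2.97; power 84%

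Simulation (4000 trials per setting) gave 67% and 85%. For d = 0.6 it gave about 100%.

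**6. Interaction.**

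| True arm difference, post-test → follow-up | r = 0.5 | r = 0.7 |
|---|---|---|
| 0.3 → 0.3 | 5.8% | 4.4% |
| 0.6 → 0.6 | 4.4% | 4.7% |
| 0.3 → 0 | 55% | 77% |

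The entries are simulated rejection rates. The first two rows are alpha with simulation error. The formula for the third row agrees: 0.3/0.1414 = 2.12 gives 56%, and 0.3/0.1095 = 2.74 gives 78%.

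**7. If pretest was meant as a time level.** With three outcome time points and no baseline covariate, the interaction has 2 degrees of freedom and does carry a sustained effect. At 100 per arm and d = 0.3 held, simulated power is 48% (r = 0.5) to 70% (r = 0.7). That model contradicts the stated baseline covariate.

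**8. The expected decline from pretest to post-test.** In the stated model pretest is not a time level, so this decline cannot be a time effect.

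**The case against.** **Other between-arm comparisons are planned.** The section provides least significant difference contrasts on estimated marginal means, and the Abstract names a MANOVA. A reader might infer that a durable, effective programme would be declared ineffective. The documents do not support that, because these analyses could show the effect. What remains is that the contrasts are not named in the Benjamini-Hochberg rule and state no visit or interval.

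**Pretest may have been meant as a time level.** The expected decline from pretest points that way. Under that reading the interaction detects a sustained effect, even with baseline also left in as covariate. In a simulation with assumed correlations 0.6/0.5/0.6, type I error was 0.053, with power 61% for d = 0.3 and 99.7% for d = 0.6. With 0.8/0.5/0.5, type I error was 0.07. So the 5% result belongs to the model as written and not to every reading. Baseline would still be both outcome and covariate, so the text needs changing either way.

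**A zero interaction needs a stable control arm.** This is correct. The expectation of no later change refers to the prevention condition, and nothing similar is said of the waitlist. If waitlist scores move after post-test, the interaction is not zero.

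**A fading benefit.** The last row of the table might suggest that such a programme would be declared effective. The section states the expected direction, a steeper decline in the prevention group. A fade has the opposite sign, and the planned marginal means would show it.

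**Two further inferences do not hold.** Selection on a high OCI-R score suggests that within-group d is inflated by regression to the mean. However, selection uses the screening form, and baseline is assessed after randomisation, so no size can be put on this from the documents. Nor does the text say that a non-significant change after post-test proves maintenance. It states only an expected result.

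**Conclusion.** The point holds for the model as written. The error-controlled p-values answer whether the arm difference changes between post-test and follow-up, and superiority is not that question. With a held benefit and a stable control arm, they are significant in about 5% of trials at any effect size and any correlation. The baseline-adjusted difference at post-test would have roughly 67% to 85% power for d = 0.3 at 100 per arm. That range rests on assumed correlations of 0.5 to 0.7 and no dropout.

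The fault is a misdirected and internally inconsistent significance rule. It does not show that the trial cannot demonstrate efficacy. The planned contrasts can supply the right quantity once they are named and brought under the rule.

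**What to change.** Keep the mixed model and change the test.

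1. For each primary outcome, name the baseline-adjusted between-arm contrast at a pre-stated visit as the efficacy test. Under the stated coding, the post-test contrast is the treatment coefficient, and the follow-up contrast is that coefficient plus the interaction. Whether to use post-intervention, follow-up or both is the sponsor's choice. If follow-up is named, its timing must be settled first, since the Abstract says one year and the outcome measures section says six months.
2. Apply Benjamini-Hochberg to those contrasts.
3. Report the interaction only as a description of durability.
4. Report the adjusted between-arm difference with its 95% confidence interval alongside the within-group d.

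Alternatively, if pretest was meant as a time level, keep baseline in the outcome vector, remove it as covariate, and state the between-arm contrasts of change from it.

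The cost is wording only, with the same data and software. The Trial status section says analysis starts once the primary endpoint data are complete, so if that point has not been reached the change can be recorded before any analysis.

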## Methods

### Study design and ethical aspects

We will conduct a single-blind (blinded outcome assessors), randomized (1:1), controlled, parallel-group, superiority trial comparing the ØCD prevention program with a control group (waitlist) for adults at risk of OCD. The study is registered on clinicaltrials.gov (ID: NCT06262464). All quality and safety aspects will be regularly monitored by an external party: the University Ethical Review Board, and by the financing authority of the project (National Authority for Scientific Research). The study has been approved by the University Ethical Review Authority (937/28.11.2023). Potential protocol modifications will be described in detail on clinicaltrials.gov. We used the SPIRIT reporting guidelines [6].

Participants will be asked to provide informed consent before baseline assessment. They will receive detailed information about the study and their right to withdraw from the study without the obligation to give reasons. We do not expect major relevant risks for participants during the study, or after the study is completed. The time burden for the participants will be a reasonable amount. The data collection and storage will be conducted according to GDPR legislation, and all personal data will be securely stored on the University’s encrypted servers, following the set data management guidelines.

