### Inclusion and exclusion criteria

Participants are included if they are of legal age (above 18). We include participants who have an OCI-R [10] score at or above the cut-off point on the OCD subscale (≥ 12). Exclusion criteria are as follows: (1) clinically diagnosed OCD, (2) current psychiatric/psychotherapeutic treatment, (3) a personality disorder diagnosis, and (4) suicidal ideation.

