### Primary outcome measures

#### Obsessional Compulsive Inventory - Revised (OCI-R; [10])

OCI-R is a self-report questionnaire of 18 items, and it measures OCD symptoms across six subscales: washing, checking, neutralising, obsessing, ordering, and hoarding. OCI-R was used in the initial screening of eligible participants, where the OCD subscale (which excludes the hoarding component) was used to determine participants who are at risk of developing OCD symptoms (cut off point (≥ 12). For the present study, the reduction in OCI-R OCD subscale assessment is the primary outcomes.

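### The only effect size the plan names is a within-group Cohen's d, which does not estimate the between-arm contrast that the trial is designed to test

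*Protocol article*

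**What the plan says.** Study design and ethical aspects describes a 1:1 randomised, parallel-group "superiority trial comparing the ØCD prevention program with a control group (waitlist"), and the stated hypothesis is superiority over control.

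Under Inclusion and exclusion criteria, participants enter with an OCI-R "score at or above the cut-off point on the OCD subscale (≥ 12"). The OCI-R section under Primary outcome measures confirms that "OCI-R was used in the initial screening of eligible participants", and adds that "the reduction in OCI-R OCD subscale assessment is the primary outcomes". PHQ-9 and GAD-7 are also primary outcomes.

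The Outcome measures section places the baseline assessment after randomisation. It does not say whether the OCI-R is completed again then or carried over from the screening form.

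The Data analysis section tests efficacy between arms, through the time-by-treatment interaction in a mixed model and a least significant difference comparison of changes in estimated marginal means. It then adds: "To facilitate comparisons with other studies", Cohen's d "statistic will be calculated to determine within-group effect sizes". No between-group standardised effect is named, and no denominator is given for d. The only other d is the planning value of 0.3 under Sample size, whose type is not stated.

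**The concern.** The plan chooses an effect size that answers a different question from the trial's. A pre-post d within one arm counts every source of change over the interval, including change that would have happened on the waitlist. People who volunteer through an enrolment link and qualify by scoring high on a symptom scale tend to score lower later, with or without a programme.

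The protocol designates this d as the figure for comparison across studies, and it presents the trial as the first of its kind in OCD prevention. A reader or meta-analyst who took the programme arm's d as the effect of the programme could read benefit into change that the control arm shares. A within-group d also cannot be pooled with between-group effects from other controlled trials.

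**Working it through.** **Is there a plan figure to reproduce?** No. The article gives no expected within-group d, no retest correlation and no position of the cut-off in the recruited population. The planning d of 0.3 serves below only as a yardstick.

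**Inputs.** From the article: entry at OCI-R OCD subscale 12 or more; the same subscale as a primary outcome; baseline after randomisation. Assumed, because not given: normal scores; cut-off c population SDs above the mean; correlation r between occasions; no programme effect and no natural change. What remains is regression to the mean alone.

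**Selected group.** Mean λ = φ(c)/(1 − Φ(c)); variance v = 1 + cλ − λ². At c = 0.5, λ = 1.141, v = 0.268, SD = 0.518. At c = 1, λ = 1.525, v = 0.199, SD = 0.446.

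**Case A: fresh baseline, equal correlations.** Screening-to-baseline and screening-to-post correlations are both r. Expected baseline and post-test means are both rλ, so the drop is 0 and d = 0.

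**Case B: fresh baseline, decaying correlations.** Correlation r per step, so r² from screening to post-test. The planned mixed model itself uses a first-order autoregressive residual structure, so decay is a plausible scenario.
Drop = (r − r²)λ; baseline SD = √(r²v + 1 − r²).

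| c | r | Drop | Baseline SD | Null d |
|---|---|---|---|---|
| 0.5 | 0.9 | 0.09 × 1.141 = 0.103 | 0.638 | 0.16 |
| 0.5 | 0.8 | 0.16 × 1.141 = 0.183 | 0.729 | 0.25 |
| 0.5 | 0.7 | 0.21 × 1.141 = 0.240 | 0.801 | 0.30 |
| 1 | 0.8 | 0.16 × 1.525 = 0.244 | 0.698 | 0.35 |

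Other corners lie somewhat outside this range: c = 0, r = 0.9 gives 0.09 × 0.798/0.696 = 0.10, and c = 1, r = 0.7 gives 0.21 × 1.525/0.780 = 0.41.

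**Case C: screening score reused as pre-test.** Null d = (1 − r)λ/√v. At c = 0.5:
- r = 0.9: 0.114/0.518 = 0.22
- r = 0.8: 0.228/0.518 = 0.44
- r = 0.7: 0.342/0.518 = 0.66

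Dividing by the average of the pre and post SDs instead gives 0.20, 0.36 and 0.51.

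**Between-group d.** Both arms pass the same entry filter before random allocation, so the expected contribution of regression to the mean to the difference is 0 in every case. At 100 per arm the approximate standard error is √(2/100) = 0.141, so the 95% CI half-width is 1.96 × 0.141 = 0.28.

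**Scope.** These figures apply to the OCI-R. PHQ-9 and GAD-7 are not selected on and regress only through their correlation with it. Natural course, repeat testing and expectation enter a within-group d for all outcomes and in all three cases.

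**The case against.** The strongest reply is that d is a supplementary descriptive figure. Efficacy is judged by between-arm tests that use the waitlist and are not biased by the entry filter. The plural, effect sizes, may well mean that both arms' values will be reported. A standardised between-group difference could also be left to a fuller analysis plan, and the estimated marginal means already supply its numerator.

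Most of this stands. A reader might infer that the within-group d is the trial's headline result, or that the plan throws away the waitlist arm. The article supports neither: it attaches no efficacy conclusion to d, and its tests compare the arms.

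A reader might also carry away 0.22 to 0.66 as the size of the problem. Those values require the screening score to be the pre-test, and the Outcome measures section reads more naturally as a fresh baseline. They also depend on dividing by an SD narrowed by selection. The comparison with 0.3 is loose too, since the type of that d is not stated.

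What does not stand is the appeal to an unseen plan. The article does not leave the effect size open. It names one, assigns it to cross-study comparison, and the one named does not estimate the trial's contrast. Showing it for both arms would help, but two within-arm values are still not an effect estimate with an interval.

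**Conclusion.** The concern holds for the reported effect size and not for the hypothesis tests. The one standardised effect named for comparison with other studies contains change that is unrelated to the programme. That is so whichever score serves as pre-test.

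The part due to regression to the mean on the OCI-R cannot be fixed from the article. On the natural reading of a fresh baseline it runs from about 0 to roughly 0.15 to 0.35, depending on whether correlations decay and where the cut-off falls. It would be about 0.2 to 0.7 if the screening score were reused with a cut-off 0.5 SD above the mean and the baseline SD as divisor. Confidence is high on the mismatch between effect size and design, and low on any single figure. It is worth correcting because the change costs little; it does not threaten the primary comparison.

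**What to change.** In Data analysis, replace the Cohen's d sentence with one to this effect: for each outcome, the effect size is the between-group standardised difference at post-test and at follow-up, meaning the baseline-adjusted difference in estimated marginal means divided by a prespecified SD (for example the pooled baseline SD), with its 95% CI. Within-group d is descriptive only and shown for both arms. The pre-test score comes from the baseline assessment, not from the screening OCI-R.

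The entry cut-off also narrows the baseline SD, so the SD used should be reported for readers who need to rescale.

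The cost is one sentence. The planned mixed model already yields the marginal means, and no new model is required. If the OCI-R is not in fact completed again at baseline, that should be stated. The reported d will probably be smaller than the within-group value.

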### Sample size

G*Power was used for the sample size calculation and, following an effect size of d=0.3 with a n alpha level of α = 0.05 and power of 0.95, a sample size of 175 was suggested. Based on this power analysis and expected drop-out rates, we aim for 200 participants (100 per treatment arm). The Consolidated Standards of Reporting Trials flow chart of the trial is shown in Figure 1.

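### The predictors named for imputation above 10% missing data omit treatment arm and post-test scores; if the imputed scores enter the arm comparison, the effect shrinks by about the missing share

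*Protocol article*

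**What the plan says.** All statements are in the protocol article.

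- **Main analysis** (Data analysis): "Given the anticipated dropout rate, mixed models will be employed as the most suitable statistical method". The approach is described as "accounting for the dependency between observations and handling missing data effectively".
- **Analysis model** (Data analysis): "Fixed effects in the model will include time, treatment, and their interaction". The models are adjusted for baseline. The next relevant sentence is "In cases of missing data, these variables will also be included as fixed effects"; it does not make clear which variables it means.
- **Time coding** (Data analysis): "Time will be treated categorically, with the first post-baseline measurement serving as the reference category". The time-by-treatment interaction is what is tested across outcomes.
- **Imputation rule** (Data analysis): "In cases where the proportion of missing data exceeds 10%, maximum likelihood imputations will be performed based on demographics and pretreatment scores". It follows the sentence on within-group effect sizes. It does not say whether imputation is single or multiple, which analysis uses the result, or how the proportion of missing data is counted.
- **Dropout** (Sample size): "Based on this power analysis and expected drop-out rates, we aim for 200 participants", up from 175. No dropout percentage is given; the Article summary calls the expected rate moderate.

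**The concern.** A likelihood-based mixed model already uses every observed visit and is valid under missing-at-random if correctly specified. The imputation rule adds a step in front of it that can only do worse as described. An imputation model that omits treatment arm assumes that arm makes no difference to the missing scores, which is the very question of the trial. Omitting the post-test score also discards the best available information about a participant who completed post-test but missed follow-up.

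The sentences on fixed effects do not repair this, because they describe the analysis model and not the imputation model. At stake are the size of the estimated effect, its apparent persistence to follow-up and, depending on the type of imputation, the width of the intervals.

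**Working it through.** **Inputs from the article.** 100 per arm, 1:1 allocation; effect 0.3 SD; 175 raised to 200; imputation trigger 10%; imputation predictors demographics and pretreatment scores.

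**Assumed inputs.** Missing share m of 12.5%, 20% or 30%, equal in both arms; data missing completely at random; correlations baseline–post 0.6, baseline–follow-up 0.5, post–follow-up 0.7; comparison at follow-up adjusted for baseline.

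**1. Implied loss.** 1 − 175/200 = 12.5% of participants. Only this ratio is used here. (The 175 does not itself reproduce as a two-arm comparison at d = 0.3 with 95% power, which needs 289 per arm two-sided. That is a separate matter and does not affect this point.)

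**2. Is 10% crossed?** Counted per visit, 12.5% exceeds 10%. Counted over scores at three visits with baseline complete, 12.5% of participants missing both later visits gives 2 × 12.5%/3 = 8.3%, and missing follow-up alone gives 12.5%/3 = 4.2%. Both are below 10%.

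**3. Shrinkage.** Observed participants differ between arms by δ. Imputed participants, predicted from one common regression, differ by 0 on average. The expected difference is (1 − m)δ + m × 0 = (1 − m)δ.

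| m | (1 − m) × 0.30 | Simulated estimate |
|---|---|---|
| 12.5% | 0.2625 | 0.261 |
| 20% | 0.240 | 0.239 |
| 30% | 0.210 | 0.211 |

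The same factor appeared with single deterministic, single stochastic and multiple imputation. It also held at 20% missing with correlations from 0.3 to 0.8.

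**4. Precision.** The standard error with no missing data is 0.123.

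| m | Observed data only | Single filling, no arm | Multiple imputation, no arm | Multiple imputation with arm and post-test |
|---|---|---|---|---|
| 12.5% | 0.131 | 0.115 | 0.132 | 0.129 |
| 20% | 0.138 | 0.110 | 0.137 | 0.134 |
| 30% | 0.147 | 0.103 | 0.144 | 0.142 |

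- *Single filling:* coverage of the true effect is about 93–94%, 91–92% and 86%. Estimate and standard error shrink together, so power is unchanged from the observed-data analysis (62.1% against 62.2% at 12.5%).
- *Multiple imputation without arm:* the standard error is about 1.13, 1.24 and 1.37 times the true sampling SD, with coverage of 96–97%.
- *Multiple imputation with arm and post-test:* the effect is recovered (ratio to truth 1.00–1.01) with coverage of about 94–95%.

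**5. No true effect.** With single filling the rejection rate stays near 5–6%. With 10% missing in one arm and 30% in the other it was 5.4% for single filling and 1.7% for multiple imputation without arm.

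**6. Time-by-treatment contrast.** Suppose the effect is stable and only follow-up scores are missing. The follow-up difference is (1 − m)δ and the post-test difference is δ, so the contrast shows a false waning of mδ: 0.0375, 0.06 and 0.09 (simulated 0.039, 0.061 and 0.091). A test of waning then rejects in 6.5%, 8.3% and 12.6% of trials, against about 5% with complete data.

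**The case against.** The article is a condensed account. Naming two groups of predictors does not prove a closed list, and a fuller specification may exist. It also never says that the imputed data feed the primary mixed model. The position of the sentence would allow it to serve the within-group effect sizes only, where the distortion is smaller: at 12.5% missing, the simulated mean improvement in the prevention arm falls from 0.30 to 0.28. At the implied loss of 12.5%, even the between-arm bias is small and conservative. These points stand, and they make the concern conditional on how the rule is used. They do not remove it: the one imputation rule that the article states names predictors that leave out arm, and nothing else shown adds it.

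A reader might infer more than the text supports:

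- *Intervals will be too narrow.* This holds only for single imputation. It may be the natural reading, since no pooling is mentioned, but under multiple imputation without arm the intervals are too wide.
- *The plan itself predicts that the 10% trigger will be met.* It gives no dropout percentage and does not define the proportion. Step 2 of the working shows that the answer depends on the counting.
- *The error rate for a true null is inflated.* It is not.

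The calculations also use a baseline-adjusted comparison at follow-up and a simple post-to-follow-up contrast, not the planned AR(1) model.

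**Conclusion.** The concern holds in conditional form. If the rule is followed as written and the imputed scores enter the arm comparison, the effect is diluted by about the missing share. That is 0.30 to about 0.26 at the 12.5% loss implied by the recruitment target, and to 0.24 or 0.21 at the assumed rates of 20% or 30%. If only follow-up is missing, a stable effect also appears to wane by about 0.04, 0.06 or 0.09 SD. This bears on the plan's expectation that gains are maintained from post-test to follow-up.

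The direction and the (1 − m) factor do not depend on the type of imputation; the effect on standard errors does. The sizes rest on data missing completely at random and equal missing shares in the two arms. The standard errors and coverage also depend on the assumed correlations. It is plausible, but not stated, that the trigger will be met. The rule is worth changing because it gives a worse answer than the method already chosen for missing data.

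**What to change.** Delete the 10% imputation rule. State that the primary analysis is the likelihood-based mixed model fitted to all observed data, with no prior imputation.

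If imputation is kept as a sensitivity analysis, specify multiple imputation with treatment arm and all observed outcome time points in the imputation model, alongside demographics and baseline scores.

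Deleting the rule removes a step and costs nothing. Keeping multiple imputation adds a little analysis work. In either case the intervals will be wider than single imputation would give. The change should be made before outcome data are examined by arm.
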